### Objectives

The study aims to show that systematic screening leads to earlier detection of diabetic retinopathy (DR) and reduces visual impairment. It will compare the effectiveness of screening at physician clinics versus routine DR care in eye care settings. The screening program, supported by trained non-medical technicians, is AI-enabled and targets over 90% accuracy in appropriate referral of DR and 80% coverage of eligible people with diabetes (PWD).

The secondary objectives of the study are to: 1. Assess the cost-effectiveness of the AI-enabled systematic screening program and referral pathway compared to the current pathway at an eye care clinic. 2. Evaluate patient satisfaction and adherence to follow-up recommendations in the AI-enabled screening program versus the routine care pathway through an effective digital tracking system.

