## Methods and analysis

### Study design

We will conduct a prospective cohort study involving a comparison between two patient groups: (i) intervention cohort: patients screened at the diabetes clinics using AI and trained nonmedical technicians and referred to the eye clinic as per the proposed pathway, and (ii) standard-of-care (SOC) cohort: patients who arrive at the ophthalmology clinic as per current practice - either self-walk-ins or referrals from other healthcare providers. Fig 1 shows SPIRIT template for clinical trial.

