### Statistical analysis

Accuracy of AI-enabled cameras: Taking the grading of images done by the experts as the ground truth, we will estimate the accuracy of the AI- enabled cameras (operated by a non- ophthalmic technician) using standard measures such as sensitivity, specificity, and area under the ROC (Receiver Operating Characteristic). Multivariable regression models will be employed to adjust for potential confounders, including age, diabetes duration, baseline visual acuity, and other relevant factors. These models will allow for a more accurate assessment of the relationships between the intervention and key outcomes, such as disease staging at diagnosis, referral rates, and long-term visual outcomes, by accounting for the influence of these confounders. Both linear and logistic regression models will be used, depending on the nature of the outcome variable, to ensure robust and reliable results. Additional statistical tests, such as chi-square tests for categorical outcomes and t-tests or ANOVA for continuous outcomes, will be employed as appropriate.

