### Sample size

We calculate the sample size to detect meaningful differences in the disease staging of patients between two arms at their first eye consultation. Based on the historic data from LVPEI, we assume a 50% prevalence of STDR among DR patients in the SOC arm. Also, we assume that the prevalence of STDR in the intervention arm at the time of screening in the diabetes clinic would be much lower (approximately 10%). However, patients in early stages of DR may not comply with the referral and hence the prevalence of STDR among patients who complete their first ophthalmology visit may be higher (approximately 25%). Based on these estimates, to achieve a power of 80% with a Type-I error rate of 5%, we estimate a sample size of 60 patients in each arm. Since the additional intervention required for the study is minimal (a short check-up using a camera), we expect that about 80% of the eligible patients will consent to participate. Thus, we will need 75 patients with DR to be identified in the intervention arm. Further, based on the historic data at the IDEA clinics, we estimate that 20% of all new registering diabetic patients will have DR. Thus, we will plan to register and screen 375 new diabetic patients each at IDEA clinics (intervention) and LVPEI clinics (SOC arm).

To evaluate the AI tool’s diagnostic accuracy with sensitivity and specificity set at 80%, a sample size of 246 DR-positive cases is required for sensitivity analysis, and 246 DR-negative cases for specificity analysis, assuming a 95% confidence level and a margin of error of ±5%.Given the estimated 20% prevalence of diabetic retinopathy (DR) in the screened population, a total of 1230 patients will be screened to ensure adequate representation of both DR-positive and DR-negative cases.

To assess patient satisfaction, a sample size of **316 patients** will be selected from both the AI-enabled and routine eye care pathways, calculated to detect a difference in satisfaction rates (80% vs. 65%) with a **95% confidence level** and a **margin of error of ±5%**. Random sampling will be employed to ensure unbiased selection of participants from each pathway. This method will involve assigning unique identifiers to eligible patients and using a randomization tool to select participants, ensuring the sample is representative of the study population.

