### Process evaluation

The process evaluation will focus on several key metrics to assess the effectiveness and efficiency of the AI-enabled systematic screening program. These metrics include the DR detection rate and STDR detection rate, which will measure the program’s ability to identify diabetic retinopathy and sight-threatening diabetic retinopathy, respectively. Visual outcomes, specifically visual impairment (VI) and blindness, will be tracked to evaluate the impact of the program on patient health. The timely referral rate for screening, defined as referrals made within two weeks of contact with eligible PWD for DR screening, and the timely referral rate for management, defined as referrals made within two weeks of contact with eligible PWD diagnosed with STDR, will be measured to ensure prompt follow-up and treatment. Additionally, the treatment uptake rate and follow-up rates will be monitored to gauge patient adherence to recommended care. Lastly, a cost-effectiveness analysis will be conducted, considering both direct and indirect expenses, to determine the financial viability and benefits of the program.

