Provider satisfaction	Proportion of healthcare providers reporting satisfaction with the AI-assisted DR screening program.	Number of providers reporting satisfaction	Total number of providers who completed the satisfaction survey
Follow-up rate	Proportion of patients who return for follow-up visits after initial DR screening or referral.	Number of patients who return for follow-up visits	Total number of patients advised to return for follow-up visits
Long-term outcomes	Proportion of patients with improved visual outcomes or stable DR over a defined period after screening or treatment.	Number of patients with improved visual outcomes or stable DR over time	Total number of patients tracked for long-term outcomes

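### The single follow-up rate in Table 1 spans the step from referral to first eye-clinic attendance in the screening arm only, so the planned between-arm adherence comparison is not like for like

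*Protocol article*

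**What the plan says.** Table 1 (Program outcomes) has one follow-up indicator: "Proportion of patients who return for follow-up visits after initial DR screening or referral". Its denominator is "Total number of patients advised to return for follow-up visits". Under Process evaluation, "follow-up rates will be monitored to gauge patient adherence to recommended care".

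The second secondary objective (Objectives) is comparative. It covers "adherence to follow-up recommendations in the AI-enabled screening program versus the routine care pathway".

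The arms enter at different places (Study design). The intervention cohort is "patients screened at the diabetes clinics using AI and trained nonmedical technicians and referred to the eye clinic as per the proposed pathway". The SOC cohort is "patients who arrive at the ophthalmology clinic as per current practice - either self-walk-ins or referrals from other healthcare providers". Study procedures places follow-up appointments at LVPEI.

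The Sample size section expects that "patients in early stages of DR may not comply with the referral". It takes the share of STDR among patients with diabetic retinopathy (DR) in the intervention arm as about 10% at screening and about 25% among those who complete a first ophthalmology visit. In the SOC arm it assumes 50%.

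The Statistical analysis section relates the intervention, by regression, to outcomes that include "disease staging at diagnosis, referral rates, and long-term visual outcomes".

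**The concern.** In the screening arm, the first visit to LVPEI after screening or referral is the patient's first attendance at the eye clinic. In the SOC arm that attendance is the condition for being in the study. A patient who was referred by another provider and never arrived is not in the SOC cohort, whereas the same patient in the screening arm stays in the denominator.

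The two rates therefore cover different stretches of the care pathway. The comparison could show a difference in adherence when patients in both arms behave identically once they are at the eye clinic. Adjustment for age, diabetes duration and visual acuity cannot repair a difference in what is counted.

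The referral rate has a related problem. Referral from screening to the eye clinic has no like-for-like counterpart in SOC patients, who are already there.

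**Working it through.** **The plan's own figure.** The plan states no expected follow-up rate. The inputs used here (50%, 25%) come from its sample size, so that was reproduced first. For 50% versus 25%, two-sided 5%, 80% power, pooled variance:

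n = [1.960 × √(2 × 0.375 × 0.625) + 0.842 × √(0.25 + 0.1875)]² / 0.25² = 57.7, so 58 per arm.

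The stated 60 agrees (power at 60 per arm is 81.6%). Then 60/0.8 = 75 and 75/0.2 = 375, as stated.

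**Step 1: one rule, two entry points.**
- Screening arm: screened at IDEA, referred, first LVPEI visit, later LVPEI visits. The rate starts at screening or referral, so the first LVPEI visit lies inside the measured stretch.
- SOC arm: arrival at LVPEI, enrolment and screening there, later LVPEI visits. First attendance is 100% by enrolment and lies before the measured stretch.
- Table 1 has no separate referral-completion row; its referral rate counts referrals made. The Ethics section keeps patients lost to follow-up in the analysis. Non-attendance after referral can therefore appear only in the follow-up rate.

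**Step 2: first attendance implied by the plan.** Let c be the share of STDR patients who attend and a the share of all DR patients who attend. The STDR share among attenders is 0.10 × c / a. Setting this to 0.25 gives a = 0.10 × c / 0.25.
- c = 100%: a = 40%, and attendance of DR patients without STDR is (0.40 − 0.10)/0.90 = 33%
- c = 80%: a = 32%
- c = 50%: a = 20%

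So 40% is a ceiling. It rests on two approximate figures and covers DR patients only. Patients referred for poor acuity, other pathology or ungradable images are outside it.

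**Step 3: illustration of the artefact.** Assume the same return rate r after an attended eye visit in both arms, so that the true difference is zero. Table 1 allows two scorings of the screening arm. Under A, first attendance counts as the return, and the difference from SOC is a − r. Under B, the patient must attend and then return, and the difference is a × r − r.

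| a | r (assumed) | A, points | B, points |
|---|---|---|---|
| 40% | 50% | −10 | −30 |
| 40% | 70% | −30 | −42 |
| 40% | 90% | −50 | −54 |
| 80% | 70% | +10 | −14 |

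Under B the difference is −r × (1 − a), which is never positive. Under A it is positive whenever a exceeds r.

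**The case against.** The strongest reply is that Table 1 nowhere prescribes different counting by arm. It speaks of patients who return among those advised to return. The Sample size section names the first ophthalmology visit and compliance with referral separately, and Study procedures ties the 3, 6 and 12 month follow-up to the diagnosis. One could read the row as covering only those scheduled visits, in both arms. An analysis plan that is not shown might also fix the index visit.

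Part of this stands. A reader might infer that the protocol itself lays down first attendance for one arm and return visits for the other. It does not; the mismatch follows from applying one rule to two entry points. But the narrower reading does not fit a clock that starts at screening or referral, or a denominator that is not limited to attenders. This is a stated rule, not one left to be filled in later.

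A reader might also infer that the comparison is bound to show worse adherence under screening, by 30 to 42 points. The documents do not support that. The 70% is an assumption, the range joins two scorings, the 40% is back-calculated, and the sign can reverse.

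Nor is it right that SOC has no referral value at all. Table 1 also counts referral for treatment, and Process evaluation defines timely referral for management after an STDR diagnosis. Such events can occur in both arms.

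Finally, loss after referral is a legitimate part of how a pathway performs, and a comparison of attenders alone would hide it. That stands, and it shapes the fix.

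**Conclusion.** The concern holds in this form: the follow-up rate as defined includes the step from diabetes-clinic referral to first LVPEI attendance in the screening arm, while SOC patients have passed that step by enrolment. The between-arm comparison in the second secondary objective is therefore not like for like.

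The plan's own figures make a lower screening-arm rate the more plausible direction, since first attendance among referred DR patients would be at most about 40%. Neither size nor sign is fixed by the document. The figures in points are illustrations that depend on the assumed return rate, the attendance reached and the scoring chosen.

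For referral rates the conclusion is narrower: referral from screening to the eye clinic is not comparable between arms, but a referral event defined in both could be.

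The change should be made, but it concerns a secondary outcome and leaves the 60-per-arm calculation on disease staging untouched.

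**What to change.** Split the follow-up row of Table 1:

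1. Referral completion: the share of referred patients who attend a first LVPEI visit, reported for the intervention arm only.
2. Follow-up adherence: the share of patients seen at a first LVPEI consultation who attend the next advised visit, defined identically in both arms and used for the between-arm comparison.

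Adjust (2) for DR stage at that consultation. By the plan's figures, attenders with DR differ in severity (about 25% STDR against 50% in SOC), and the follow-up interval depends on diagnosis. Present (1) beside (2) so that loss along the pathway stays visible.

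In Statistical analysis, do not model referral from screening to the eye clinic as a between-arm outcome. Report it within the intervention arm, and compare arms only on a referral event defined for both, such as referral for treatment after the first LVPEI consultation.

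The first eye consultation is already the anchor for the staging comparison in the Sample size section. The cost is wording, with no evident new data, because Data management and Process evaluation already provide for tracking DR patients and their follow-up. The downside is that the adherence comparison is restricted to patients who reached LVPEI, which selects on an event after entry in the screening arm. Stage adjustment reduces that problem but cannot be relied on to remove it.

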### Ethics

The proposed study will comply with the ethical principles of research. The study will commence following approval and clearance from the Institutional Ethics Committees (IEC) of LV Prasad Eye Institute and IDEA Clinics. The Ethics Committee of LV Prasad Eye Institute approved the study on 06/10/2023, and the Tanvir Hospital Institutional Ethics Committee for Biomedical and Health Research granted approval on 07/11/2023.Any protocol amendments/modifications will be implemented only after Institutional Ethics Committee clearance. Informed written consent will be sought from all the patients after providing the necessary information regarding the study objectives as well as potential benefits and risks of participating in the study. They will also be informed that they can withdraw from the study at any point prior to, during or after the data collection. They will have the freedom to ask any queries pertaining to any aspect of the study. Confidentiality will be maintained and all the information regarding the participants will be protected under all circumstances. At LVPEI, The patients written consent for comprehensive examination done at LVPEI will be considered as study consent form.

All participant data will be anonymized to ensure confidentiality. Unique identification codes will be assigned to participants, and no personally identifiable information (PII) will be linked directly to the dataset. Data will be securely stored in encrypted digital formats on password-protected servers with access restricted to authorized personnel. Hard copies, if any, will be stored in locked cabinets within secure facilities. Any data transfer between study sites will be conducted using secure, encrypted channels to maintain data security.

Participants who withdraw from the study will have their data excluded from subsequent analyses unless explicit consent is provided for its continued use. Patients lost to follow-up will be included in an intention-to-treat analysis to minimize bias and preserve the benefits of systematic recruitment. Sensitivity analyses will be performed to evaluate the potential impact of missing data. Where applicable, missing data will be addressed using appropriate imputation methods, such as multiple imputation or the last observation carried forward, to ensure the robustness and validity of the study findings.

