The images captured at each physician clinic facility will be transferred through a cloud-based teleophthalmology system to the LVPEI central image reading centre (LILAC (L V Prasad eye institute Image Laboratory and Analysis Centre), where grading will be done by two trained graders. Final grading of all referable cases of DR, ungradable images, other pathology needing referral, and an audit of 5% of normal fundus images will be conducted by an experienced ophthalmologist. Patients diagnosed with DR will be referred for appropriate treatment and provided with follow-up advice. Follow-up appointments will be arranged at LVPEI.The follow-up periods for individual participants will be based on the diabetic retinopathy diagnosis and scheduled at 3, 6, and 12 months intervals.

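### Last observation carried forward is permitted although an unchanged grade counts as long-term success, so patients lost without recorded worsening would be scored as successes

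*Protocol article*

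**What the plan says.** The last paragraph of the Ethics section sets out how incomplete data are handled:

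- Loss to follow-up: "Patients lost to follow-up will be included in an intention-to-treat analysis to minimize bias".
- Withdrawal: "Participants who withdraw from the study will have their data excluded from subsequent analyses unless explicit consent is provided".
- Imputation, where applicable: "missing data will be addressed using appropriate imputation methods, such as multiple imputation or the last observation carried forward".
- Robustness: "Sensitivity analyses will be performed to evaluate the potential impact of missing data". Their content is not given.

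Table 1 (Program outcomes) defines the long-term outcome as "Proportion of patients with improved visual outcomes or stable DR over a defined period after screening or treatment". Its numerator is "Number of patients with improved visual outcomes or stable DR over time" and its denominator is "Total number of patients tracked for long-term outcomes". Under Study procedures, follow-up depends on the diagnosis and is "scheduled at 3, 6, and 12 months intervals".

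No passage says which imputation method serves which outcome. No passage gives an expected loss rate or an expected rate of stable disease.

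**The concern.** Diabetic retinopathy can progress, and the favourable result in Table 1 includes no change. LOCF imputes no change from the last visit attended. For this outcome it therefore writes a success into the record of any patient whose last available grade shows no worsening. Improved vision is not needed as well, because the definition joins the two criteria with an or.

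The method acts on patients lost to follow-up, who stay in the analysis and need a value. It does not act by default on those who withdraw, whose data are removed.

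At stake is the long-term success rate in each arm and, where loss or unrecorded progression differs between arms, the comparison of the two. The outcome has some weight: reducing visual impairment is part of the primary objective, and the Statistical analysis section names long-term visual outcomes among the key outcomes.

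**Working it through.** **The plan's own figure.** The document gives no number for the long-term outcome. Its nearest stated figure is 60 per arm (Sample size), for sight-threatening disease of 50% against 25% at the first eye consultation, with 80% power and 5% type I error (two-sided assumed). The pooled two-proportion formula gives

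n = [1.96 × √(2 × 0.375 × 0.625) + 0.842 × √(0.25 + 0.1875)]² / 0.25² ≈ 58 per arm.

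This agrees with 60, where power is 81.6%. The figure concerns the first consultation, so LOCF over later visits does not touch it.

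**Inputs, all assumed.**

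- s: true rate of improved or stable disease, taken as equal in lost and retained patients unless stated.
- d: proportion lost to follow-up.
- g: share of progressors among the lost whose worsening was recorded before loss.

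**Formula.** Success under LOCF = (1 − d)s + d[s + (1 − s)(1 − g)] = s + d(1 − s)(1 − g). The overstatement is d(1 − s)(1 − g).

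**Within one arm, d = 30%.**

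| s | g = 0 | g = 0.5 | g = 1 |
|---|---|---|---|
| 60% | 0.30 × 0.40 = 12 points | 6 points | 0 |
| 80% | 0.30 × 0.20 = 6 points | 3 points | 0 |

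**Between arms, s = 70% in both, so the true difference is zero.**

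| Loss, arm A / arm B | g | Apparent success, A / B | False difference |
|---|---|---|---|
| 20% / 20% | 0 | 76.0% / 76.0% | 0 |
| 10% / 40% | 0 | 73.0% / 82.0% | 9.0 points |
| 10% / 40% | 0.5 | 71.5% / 76.0% | 4.5 points |
| 15% / 40% | 0 | 74.5% / 82.0% | 7.5 points |

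For illustration, take 60 per arm and a normal-approximation two-proportion test. The 9-point false difference would be declared significant with probability 21.7% instead of 5%, and the 4.5-point difference with probability 8.6%.

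**When the lost differ from the retained.** The overstatement in an arm is d times the share of lost patients who truly progressed without a record of it. Suppose 40% are lost in the intervention arm but, being early-stage, only 10% of them progress: 0.40 × 0.10 = 4.0 points. Suppose 15% are lost in the standard-of-care arm and 30% of them progress: 0.15 × 0.30 = 4.5 points. The net bias is then 0.5 points against the intervention, although its loss is much the higher.

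**The case against.** LOCF is one of two examples, to be used where applicable. Multiple imputation is named first, and sensitivity analyses are promised. Nothing assigns LOCF to the long-term outcome, and the choice of method by endpoint is commonly left to an analysis plan. This stands as a limit: the bias is permitted, not certain. It does not remove the point, because the protocol positively names as appropriate a method that is unsuitable for an outcome where no change is success.

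Three stronger readings are tempting, and the document does not support them.

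- A reader might infer that every lost patient becomes a success. With visits at 3, 6 and 12 months, a patient whose worsening was recorded before loss is carried forward as a failure.
- A reader might infer that LOCF favours the intervention, because the Sample size section expects early-stage patients to skip the referral. That remark concerns the first eye visit, not attrition over the following year, and says nothing of later loss under standard care. Early-stage patients may also be more stable, and the last calculation shows that this can reverse the direction.
- A reader might infer that the Table 1 denominator contradicts the intention-to-treat statement. The word tracked is ambiguous. It may cover everyone entered into tracking, and the Data management section speaks of tracking all patients with retinopathy. It may instead cover only those still followed. On the first reading LOCF can act on the lost patients. On the second it cannot, but the denominator then departs from the intention-to-treat statement.

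**Conclusion.** The concern holds for the long-term outcome. LOCF is a permitted method there, and it scores any patient lost without recorded worsening as a success.

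The overstatement in each arm is the loss rate times the share of lost patients with unrecorded progression: 6 to 12 points at 30% loss and 60% to 80% true success if no progression was recorded before loss, half that if half was recorded, and nothing if all was. These rates are assumptions; the document supplies none.

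The comparison between arms can be biased when loss, or progression among the lost, differs between them. Its direction and size cannot be determined from the document. The denominator is ambiguous and needs stating, but is not a proven contradiction. The point warrants correction but does not threaten the stage comparison at first consultation.

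**What to change.** 1. Remove LOCF as an option for the long-term retinopathy and visual outcome.
2. Name multiple imputation as the main method, with arm and the baseline data already collected in the imputation model.
3. Specify at least one sensitivity analysis that counts lost patients as not stable. At 30% loss and 70% true success this gives 0.70 × 0.70 = 49%, whereas LOCF with no recorded progression gives 49% + 30% = 79%. LOCF is then the best case for the lost patients, and the sensitivity analysis supplies the opposite bound.
4. State the Table 1 denominator as all patients with retinopathy due at the time point, so that it agrees with the intention-to-treat statement.

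The cost is a change of wording and a little more analysis. The reported long-term success rate will probably look less favourable. No change to recruitment, visits or sample size is needed.
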